**Fig. 3 Fig3:**
[figure not shown]
Sample size calculation

### Statistical analysis

Data analyses will be performed with a coded binary treatment indicator to preserve blinding to treatment allocation until the trial report is finalised by the writing committee. The trial primary and main secondary outcomes will be reported using intention-to-treat analyses based on all randomly assigned patients, except any who withdraw consent for use of all trial data.

Baseline variables will be summarised using descriptive statistics. The trial primary outcome and other time-to-event outcomes will be displayed as Kaplan-Meier curves and compared between treatments with Cox proportional hazards regression including, as covariates, the trial site stratification factor and patient age and sex. Sensitivity analyses will be performed using unadjusted Cox models which include a binary indicator of treatment as the only covariate, and also using multivariable Cox models including any other baseline covariates exhibiting substantial imbalance between randomisation arms. Lack of proportionality in any Cox model on testing will result in that outcome being assessed using a log-rank test and summarised using the Kaplan-Meier estimated median time to event [34]. Other secondary analyses, including assessment of the differential proportion of thromboembolic complications and mortality at specified time points, will be compared using either chi-square or Fisher exact tests, and also using logistic regression adjusting for the same covariates used in the Cox models. Results will be summarised using frequency tables, and risk ratios or odds ratios as appropriate, with 95% confidence intervals. Approximately normally distributed continuous variables (either untransformed or following log or other normalising transformation) will be compared using *t* tests, or otherwise compared using nonparametric methods (Mann-Whitney).

The differential trajectory of fibrinogen levels over time according to intervention will be assessed with fibrinogen measurements at predefined time points for each patient. Initial exploratory analyses will be conducted using a ‘summary measures’ approach [35], comparing maximum and minimum fibrinogen levels within individual patients during the acute resuscitation phase and also the maximum fibrinogen in the postresuscitation phase. Subsequently, univariable and adjusted multivariable linear regression analyses will be used to assess the differential effects on circulating fibrinogen levels of treatment allocation using a generalised estimating equation (GEE) approach with robust error estimates to account for the within-subject correlation of fibrinogen levels over time [36].

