Regardless of which approach is used fibrinogen can be replaced with plasma, cryoprecipitate (Cryo) and fibrinogen concentrate (FC) each containing different amounts of fibrinogen; 2 g/L, 8–16 g/L and 20 g/L, respectively. The low concentration of fibrinogen in plasma and the large volumes required potentially make it unsuitable for dedicated fibrinogen supplementation [23–25]. The RETIC trial (NCT01545635) comparing plasma to factor concentrate-based resuscitation has recently been terminated early after an interim analysis revealed potential harm to patients randomised to the plasma arm. Cryoprecipitate contains substantially higher concentrations of fibrinogen than plasma and is widely accepted as the standard of care for fibrinogen supplementation in severe haemorrhage [26]. However, its use is not currently supported by high-level evidence [27]. The CRYOSTAT trial reported in 2015 that early fibrinogen supplementation utilising Cryo was feasible and effectively maintained fibrinogen levels in traumatic haemorrhage [28]. The use of FC has a number of theoretical advantages including: standard dose per vial, reduced volume, viral inactivation, no requirement for ABO compatibility matching, ease of reconstitution and administration. However, in severe trauma there are no robust clinical trials to demonstrate a survival or cost-effectiveness benefit compared to Cryo [6, 25, 29].

A number of key questions regarding fibrinogen supplementation in traumatic haemorrhage remain unanswered, including: (1) What tests, if any should be utilised to guide fibrinogen therapy? (2) What is the optimal product for fibrinogen replacement? (3) What is the optimal dose of fibrinogen? and (4) What is the impact of early fibrinogen replacement on clinically important outcomes?

The objectives of this trial are to assess the feasibility of early fibrinogen replacement utilising FC compared to the use of Cryo in patients with traumatic haemorrhage and viscoelastic evidence of hypofibrinogenaemia. We hypothesise that fibrinogen replacement to reverse hypofibrinogenaemia in traumatic haemorrhage may be achieved more rapidly, and with a more predictable dose response, using FC compared to Cryo.

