### Randomisation

A computer-generated 1:1 block randomisation schedule has been produced by a statistician independent to the study, accommodating unequal recruitment across the four initial sites together with the possibility of additional trial sites. Secure, password-protected web-based randomisation will occur on patient arrival to a participating hospital trauma unit once inclusion and exclusion criteria have been assessed. Each patient will receive fibrinogen supplementation comprising either protocol-directed FC or Cryo therapy. Allocation concealment will be maintained through to the conclusion of the web randomisation process, but for practical and safety reasons, randomised trial patients and their treating health care professionals will not be blind to the trial intervention. Trial integrity will be supported by maintenance of blinding for outcome assessors and the trial statistician.

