### Intervention

After compliance with consent requirements and with the treating clinician’s approval, patients will be randomised to receive fibrinogen supplementation using either FC (Riastap®, CSL Behring GmbH, Marburg, Germany) or Cryo (Australian Red Cross Blood Service). The requirement for fibrinogen supplementation will be defined by a FIBTEM A5 (clot amplitude 5 min after clot formation) ≤10 mm together with a clinical scenario suggesting significant haemorrhage. The intervention will be performed in randomised patients as soon as possible after each FIBTEM threshold result becomes known. Patients will remain in their allocated intervention arm for the duration of their hospital admission up to 30 days. Dosing of FC and Cryo will be guided by the FIBTEM A5 result as per trial protocol (Fig. 1). FC will be administered by intravenous injection and Cryo by rapid intravenous infusion. Fibrinogen supplementation will be continued throughout the resuscitation according to protocol and as per the allocated intervention arm (Fig. 1).

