### Trial endpoints

The primary outcome is the time interval in minutes from FIBTEM analysis and clinical scenario suggesting that fibrinogen supplementation is required to the completion of the first administration of fibrinogen supplementation (FC or Cryo). It is aimed to administer the FC intervention within 30 min of fibrinogen requirement being identified. Consistent with the exploratory pilot nature of this study, multiple hypothesis-generating outcomes will be evaluated together with assessments of process feasibility, including:Effects of fibrinogen supplementation (FC and Cryo) on plasma fibrinogenTime to randomisationTime course of fibrinogen levels as measured by FIBTEM and Clauss Fibrinogen (FibC)Transfusion requirementsClinically relevant thromboembolic complicationsMortality at several time points including hospital discharge and 90 days

Detailed data collection will occur for the first 7 days of hospital admission and extended follow-up to 90 days (see the SPIRIT figure in Fig. 2). See Table 2 for full primary, secondary and feasibility outcomes.

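### The primary outcome is to be analysed in all randomised patients, but its clock starts only for those who meet a FIBTEM-plus-bleeding trigger after randomisation

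*Protocol article*

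**What the plan says.** All references are to the protocol article.

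- **Analysis set (Statistical analysis).** For the primary and main secondary outcomes, the section specifies results "reported using intention-to-treat analyses based on all randomly assigned patients, except any who withdraw consent for use of all trial data". That is the only exception. The primary outcome is shown as Kaplan-Meier curves and compared by Cox regression.
- **Entry and timing of randomisation (Patients, Table 1; Randomisation).** Table 1 contains no FIBTEM or fibrinogen criterion. "Secure, password-protected web-based randomisation will occur on patient arrival to a participating hospital trauma unit once inclusion and exclusion criteria have been assessed".
- **Trigger (Intervention).** Need is defined by a FIBTEM A5 of 10 mm or less "together with a clinical scenario suggesting significant haemorrhage". On when treatment is given, the section adds: "The intervention will be performed in randomised patients as soon as possible after each FIBTEM threshold result becomes known".
- **Primary outcome (Trial endpoints).** It is defined as "time interval in minutes from FIBTEM analysis and clinical scenario suggesting that fibrinogen supplementation is required to the completion of the first administration", whichever product is given.
- **Blinding (Randomisation).** After allocation, "randomised trial patients and their treating health care professionals will not be blind to the trial intervention".
- **Objective (Background).** The comparison is meant to apply "in patients with traumatic haemorrhage and viscoelastic evidence of hypofibrinogenaemia".
- **Sample size.** 100 patients are randomised and 100 are taken as evaluable. The SD is 14 min per arm, the difference 8 min, and power about 80%.

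**The concern.** The analysis set is fixed at randomisation, but the time origin arises afterwards and only in some patients. Someone who is randomised on arrival and never has both a low A5 and a suggestive clinical picture has no start time. Censoring does not help, because a censored patient still needs an origin from which follow-up is counted. The sentence on the analysis set therefore cannot be carried out for such patients, and the section gives no rule for them.

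Two things are at stake. First, whatever set replaces all randomised patients will be chosen after randomisation. If it is those who triggered or were treated, membership depends partly on a clinical assessment, and on whether further FIBTEM tests are ordered, at a time when staff know the allocation. The article itself gives a reason why behaviour could differ by arm: its Discussion says FC can be kept in the trauma bay, whereas large Cryo orders can strain blood banks. Second, the number of patients who contribute to the primary comparison will be below the 100 on which power was calculated.

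**Working it through.** **1. Setting the sections side by side**

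| Section | Who is covered |
|---|---|
| Background (objective) | Patients with viscoelastic evidence of low fibrinogen |
| Patients, Table 1 | Trauma with judged or predicted haemorrhage; no FIBTEM result needed |
| Randomisation | Everyone eligible, on arrival; also states that every patient will be given fibrinogen |
| Intervention, Trial endpoints | Treatment and clock only after low A5 plus clinical picture |
| Sample size | 100 evaluable out of 100 randomised |
| Statistical analysis | All randomised, apart from full withdrawal of consent |

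The Randomisation, Sample size and Statistical analysis sections are all written as if every randomised patient triggers. Nothing in Table 1 ensures that, and the Intervention section makes treatment conditional.

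**2. Reproducing the stated power**

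Inputs from Sample size: n = 50 per arm, SD = 14 min, difference = 8 min, alpha 5% (two-sided, as the interim analysis section confirms for the primary outcome).

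- Standard error = SD × √(2/n) = 14 × √(2/50) = 2.80 min.
- Power ≈ Φ(8/2.80 − 1.96) = Φ(0.897) = 81.5%. The noncentral t gives 80.8%.
- Detectable difference at 80% power = (1.96 + 0.842) × 2.80 = 7.8 min. At SD 30 it is 16.8 min.

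These agree with the stated 80%, 8 min and 17 min. The arithmetic is right if all 100 patients are evaluable.

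**3. Power when only some patients have a time origin**

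The documents give no share of randomised patients who trigger, so the shares below are assumptions. SD, difference and alpha are unchanged, and the arms are assumed to lose equally. The last column is 100 divided by the share, rounded up.

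| Assumed share evaluable | n per arm | Power (normal approx.) | Power (t) | Detectable difference, normal approx. (min) | Randomised for 100 evaluable |
|---|---|---|---|---|---|
| 100% | 50 | 81.5% | 80.8% | 7.8 | 100 |
| 90% | 45 | 77.4% | 76.5% | 8.3 | 112 |
| 80% | 40 | 72.4% | 71.4% | 8.8 | 125 |
| 60% | 30 | 60.0% | 58.6% | 10.1 | 167 |
| 50% | 25 | 52.4% | 50.8% | 11.1 | 200 |

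**4. Illustration of selection bias (all inputs assumed)**

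Suppose there is no true difference, SD is 14 min, and sicker patients trigger first and are treated faster, with a severity-time correlation of 0.3 to 0.5. By simulation, trigger shares of 65% (FC) and 55% (Cryo) give a spurious difference of 0.6 to 1.0 min, and 70% against 50% gives 1.3 to 2.1 min. Equal shares give none. This models who enters the set, not a shift in when the clock starts.

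**The case against.** Several counter-arguments have weight.

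- **The trigger is not purely a clinician's decision.** A reader might infer that a time origin exists only where unblinded staff declare a need. The documents do not support that. A5 of 10 mm or less is an assay reading, and entry already requires haemorrhage to be judged or transfusion predicted before allocation. The article does not say who assesses the clinical picture; that it is the treating staff is an inference. The scope for bias is the residual clinical element and the ordering of repeat tests.
- **The set fails only if someone never triggers.** This is strictly true, and no share is given. But eligibility admits patients merely predicted to need transfusion, with no FIBTEM criterion, so it is very likely.
- **The clock may look inconsistent.** A reader might see a conflict between timing from FIBTEM analysis and acting once the result is known. The first defines the measurement and the second says when staff should act. They are compatible, and the exact timestamp is detail that an article may leave to the full protocol.
- **An unseen SAP may define a subset.** It may, but it would then contradict a sentence that fixes the set and names its only exception. It would not be filling a gap.
- **This is an exploratory pilot sized on recruitment and budget.** That tempers the weight of the bias and power arguments. It does not make the primary analysis set workable.

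**Conclusion.** The point holds. As written, the all-randomised analysis of the primary outcome is undefined for any patient who never meets the joint trigger, and the stated power assumes that there are none. This is a stated rule that fails when followed.

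The measurable consequence is loss of evaluable patients: power falls from 81.5% to about 77%, 72%, 60% or 52% at assumed evaluable shares of 90%, 80%, 60% or 50%. These figures rest on the plan's own SD and its comparison of means, and on equal loss in both arms.

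The selection bias is real in principle, but its size cannot be derived from the documents. A reader might infer that it could produce or hide the whole 8 min difference. Nothing in the article supports a figure that large, and the illustration above, on assumed inputs, gives 0.6 to 2.1 min.

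**What to change.** In Trial endpoints and Statistical analysis, for analysis purposes only and without altering who is treated:

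1. Define the primary analysis set as all randomised patients whose first FIBTEM A5 after arrival is 10 mm or less, by allocated arm, whether or not treatment was then judged necessary or given. Restricting to the first sample matters, because later samples depend on test ordering by unblinded staff.
2. Start the clock at the recorded time of that result. The article does not say that this time is captured, so it needs confirming at each site.
3. Keep patients who die or are never treated in the set, with death before administration as a competing event.
4. Report the proportions triggered and treated by arm, and give the clinician-declared clock as a sensitivity analysis.
5. Keep all-randomised intention to treat for mortality, safety and transfusion outcomes.
6. In Sample size, restate power and detectable difference for the expected evaluable number.
7. Reconcile Background, Patients, Randomisation, Intervention, Trial endpoints, Sample size and Statistical analysis on who is studied, who is treated and who is analysed.

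**Cost.** The stated power will be lower. Patients with a low first A5 who are not treated will dilute the contrast somewhat, and those who first trigger on a later sample fall outside the primary set, though the sensitivity analysis still covers them. This changes the primary analysis population of an open-label trial with 40 of 100 patients enrolled, so it should be a dated amendment made without sight of outcomes by arm.

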**Fig. 2 Fig2:**
[figure not shown]
Fibrinogen Early In Severe Trauma studY (FEISTY) Standard Protocol Items: Recommendations for Interventional Trials (SPIRIT) flowchart

**Table 2 Tab2:** Outcome measures

Primary outcome measures:	
1. (A) Time to administration of fibrinogen administration (FC or Cryo) from time of ROTEM® analysis and clinical scenario suggesting that fibrinogen supplementation is required	
1. (B) Feasibility of administering FC within 30 min of ROTEM® and clinical scenario suggesting that fibrinogen supplementation is required	
2. Effects of fibrinogen supplementation (FC and Cryo) on fibrinogen levels as measured by FIBTEM and Clauss Fibrinogen (FibC)	
Secondary outcome measures:	
1. Transfusion requirements (in number of units) of PRBC, FFP, FC, Cryo, platelets, PCC at 4, 6, 12, 24 and 48 h	
2. Duration of bleeding episode or time until surgical haemorrhage control with no further coagulation factors	
3. Duration of mechanical ventilation	
4. Duration of ICU and hospital LOS	
5. ROTEM® (Sigma and Delta), Multiplate®, FBC, INR, APTT, FibC analysis at prespecified time points	
6. Evaluation of EXTEM CT in response to fibrinogen supplementation	
7. Adverse events: TACO, TRALI, Sepsis, MOF	
8. Thromboembolic complications	
9. All-cause mortality at 4, 6, 24 h and up to 90 days	
Feasibility outcome measures:	
1. Transfusion requirements (in number of units) of PRBC, FFP, FC, Cryo, Platelets, PCC at 4, 6, 12, 24 and 48 h	
2. Duration of bleeding episode or time until surgical haemorrhage control with no further coagulation factors	
3. Duration of mechanical ventilation	
4. Duration of ICU and hospital LOS	
5. ROTEM® (Sigma and Delta), Multiplate®, FBC, INR, APTT, FibC analysis at prespecified time points	
6. Evaluation of EXTEM CT in response to fibrinogen supplementation	
7. Adverse events: TACO, TRALI, Sepsis, MOF	
8. Thromboembolic complications	
9. All cause mortality at 4, 6, 24 h and up to 90 days	
Feasibility outcome measures:	
1. Time to randomisation	
2. FC and Cryo wastage	
3. Proportion of patients with blood sampling at all prespecified time points	
4. Number of missed patients (eligible but not enrolled)	
5. Randomisation errors	
6. Protocol violations	

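### The secondary duration outcomes (bleeding, ventilation, ICU and hospital stay) are cut short by death, and none of the planned analyses accounts for it, so an arm that differs only in having more deaths can look neutral or better

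*Protocol article*

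**What the plan says.** The Statistical analysis section of the protocol article names two families of method that could apply to a duration.

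- **Time-to-event outcomes:** "The trial primary outcome and other time-to-event outcomes will be displayed as Kaplan-Meier curves and compared between treatments with Cox proportional hazards regression", with site, age and sex as covariates. If hazards are not proportional, the outcome is instead "assessed using a log-rank test and summarised using the Kaplan-Meier estimated median time to event".
- **Continuous variables:** "Approximately normally distributed continuous variables (either untransformed or following log or other normalising transformation) will be compared using" t tests, with Mann-Whitney where normality cannot be reached.

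Table 2 lists these secondary outcomes: "Duration of bleeding episode or time until surgical haemorrhage control with no further coagulation factors", "Duration of mechanical ventilation" and "Duration of ICU and hospital LOS". The article does not say which family each belongs to.

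Death is a separate secondary outcome, "All-cause mortality at 4, 6, 24 h and up to 90 days", compared as a proportion by chi-square or Fisher tests and by adjusted logistic regression. Primary and main secondary outcomes are analysed by intention to treat, so patients who die early stay in the comparison. The only mention of censoring is in the Data and Safety Monitoring Committee section, and it concerns the interim mortality analyses. No competing-risk method, cumulative incidence or days-alive-and-free measure is named.

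**The concern.** A patient who dies on the ventilator, in ICU or in hospital has a short observed duration but has not recovered. Each planned method mishandles or hides this in its own way:

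- **Kaplan-Meier with deaths censored** treats those who died as if they would later have been discharged or extubated like those still at risk. One minus the curve, and the median read from it, then describe a setting without death. They overstate the probability and speed of leaving alive.
- **Cox with deaths censored** gives a valid cause-specific hazard ratio for discharge or extubation. Reported alone, it is silent about an arm that loses more patients.
- **Cox with death counted as the end of the stay** turns more deaths into faster completion.
- **t or Mann-Whitney tests on raw durations** score an early death as a short, good stay.

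The designers clearly expect early deaths, since mortality is scheduled at 4, 6 and 24 h and two interim analyses are devoted to it. At stake is how the duration results of this pilot are read: a shorter stay in one arm could reflect deaths rather than recovery.

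**Working it through.** **The plan's own figure.** The only related figure in the article is the power statement in Sample size, which concerns the primary outcome. With 50 per arm, a difference of 8 min and SD 14 min, the standard error is 14 × √(2/50) = 2.8 and 8/2.8 = 2.857. Power is then Φ(2.857 − 1.96) = 81.5%, or 80.8% by noncentral t. The stated approximate 80% is reproduced and is not in dispute.

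**Inputs for this point.** From the article: 100 patients, 1:1, so 50 per arm; follow-up to 90 days; the methods quoted above. Assumed, because the article gives no figures: mortality 10-20% in one arm and up to 40% in the other; the same lognormal hospital stay in both arms for survivors (median 10 days, log SD 0.9); exponential death times, independent of stay, with mean 1 day (also 5 and 10 days).

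**Raw durations, by formula.** If a fraction m dies early, before the overall median is reached, the overall median is the survivor quantile q = (0.5 − m)/(1 − m), that is 10 × exp(0.9 × z(q)).

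| m | q | z(q) | overall median, days |
|---|---|---|---|
| 0.10 | 0.444 | −0.140 | 8.82 |
| 0.20 | 0.375 | −0.319 | 7.51 |
| 0.30 | 0.286 | −0.566 | 6.01 |
| 0.40 | 0.167 | −0.967 | 4.19 |

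The gap is 8.82 − 7.51 = 1.31 days for 10% v 20%, 8.82 − 6.01 = 2.81 for 10% v 30%, 7.51 − 6.01 = 1.50 for 20% v 30%, and 7.51 − 4.19 = 3.32 for 20% v 40%. The arm with more deaths always looks better.

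**Simulation, 50 per arm, 3000 runs per row.** Hazard ratios (HR) are one-step log-rank estimates for the arm with more deaths. An HR above 1 means faster end of stay, which reads as better. The Mann-Whitney and t columns give the share of runs in which that arm is significantly better.

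| Mortality | Mean death day | Median difference, days | Mann-Whitney | t on log days | HR, death censored | HR, death ends stay | Subdistribution HR, discharge alive |
|---|---|---|---|---|---|---|---|
| 10% v 10% | 1 | 0.0 | 2.5% | 2.1% | 1.00 | 0.99 | 1.00 |
| 10% v 20% | 1 | −1.3 | 13% | 18% | 1.00 | 1.12 | 0.77 |
| 10% v 30% | 1 | −2.9 | 39% | 49% | 1.00 | 1.26 | 0.61 |
| 20% v 30% | 1 | −1.5 | 12% | 14% | 1.00 | 1.13 | 0.78 |
| 20% v 40% | 1 | −3.2 | 38% | 41% | 1.00 | 1.27 | 0.62 |
| 10% v 30% | 5 | −1.8 | 20% | 23% | 1.00 | 1.19 | 0.68 |
| 10% v 30% | 10 | −1.4 | 14% | 15% | 1.00 | 1.15 | 0.74 |

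The medians agree with the formula. With equal mortality the one-sided error is about its nominal 2.5%, so the excess in the other rows comes from mortality alone. Later deaths shrink the effect, partly because some simulated deaths then fall after discharge.

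**Kaplan-Meier.** With 10% v 30% early deaths censored and identical survivor stays, one minus Kaplan-Meier for discharge approaches 100% in both arms. In fact about 90% and 70% leave alive.

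**With death handled (10% v 30%, mean death day 1).** The subdistribution HR of 0.61 flags the arm as worse in 60% of runs. Hospital-free days to day 28, with death scored zero, are 3.0 fewer, flagged as worse in 32% of runs.

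**The case against.** The strongest reply is that the article is silent rather than wrong. It never says deaths are censored, it never assigns the durations to either family of method, and a full protocol or analysis plan that is not shown may hold the rule. It adds that these are secondary outcomes of an exploratory pilot, that mortality is reported beside them and watched at two interim analyses, and that every magnitude here is assumed.

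Much of this stands as a limit. It does not remove the point, which rests on the methods the article does name. Both families lead to a neutral or favourable result when only mortality differs, so the missing assignment does not rescue either. A death rule kept elsewhere would have to replace or supplement those methods.

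Four stronger readings are tempting and are not supported:

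- **That the Cox analysis is invalid.** With deaths censored it is a proper cause-specific hazard analysis. In the scenarios above, an HR of 1 is the correct answer to that question. The fault lies in the Kaplan-Meier curve and median, and in reporting one cause-specific hazard without the other.
- **That the primary outcome is compromised.** Time to completion of the first fibrinogen dose runs in minutes, with a planning SD of 14 min and a 30 min aim for FC. Few deaths can be expected in that window, and the document gives no figure suggesting otherwise.
- **That one product is likely to cause more deaths, or that a particular bias should be expected.** No mortality rate or difference is given. A scenario of 15% v 30% with a 20-day survivor median gives 16.4 v 12.0 days, about 27% shorter, but it is one assumed point among many.
- **That these durations will drive the larger trial.** The Discussion names transfusion requirements and mortality as examples of its outcomes, not durations.

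**Conclusion.** The point holds for the secondary durations only. As named, the analyses can present an arm with more deaths as neutral (Cox with deaths censored: HR about 1.00 in every scenario) or as better (raw durations: median stay about 1.3 to 3.2 days shorter, falsely significant in about 12-39% of runs by Mann-Whitney and 14-49% by t test). The direction follows from the methods. The size depends on assumed mortality, survivor stay and timing of death, and the bias disappears if mortality is equal. Only hospital stay was quantified. The same reasoning applies to ICU stay, ventilation and bleeding, but no figure is offered for them. Because mortality is reported alongside, an attentive reader could notice an imbalance. This is a correction worth making, not a threat to the trial's main result.

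**What to change.** For the secondary durations, state one of the following.

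1. **Competing-risk route.** Replace Kaplan-Meier curves and medians with cumulative incidence (Aalen-Johansen) of haemorrhage control, extubation, ICU discharge and hospital discharge, with death as a competing event. Report cause-specific hazard ratios for both the event and death. The planned Cox models already supply the first of these if deaths are censored.
2. **Free-days route.** Analyse ventilator-, ICU- and hospital-free days to a fixed day within the 90-day follow-up, with death scored worst, and show mortality and survivor duration separately. Bleeding and haemorrhage control would still need the first route.

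The cost is wording and slightly more analysis. Mortality to day 90 is already collected, so no new patients are needed. Free-days blend death with duration, which is why the components must be shown. The primary outcome analysis, sample size and power are unaffected.
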